# Is the addition of running retraining to best standard care beneficial in runners with medial tibial stress syndrome? Protocol for a randomised controlled trial

**DOI:** 10.1002/jfa2.12029

**Published:** 2024-06-14

**Keywords:** gait retraining, leg injuries, prevention, randomized controlled trial, running injuries

## Abstract

**Background:**

Running retraining is commonly used in the management of medial tibial stress syndrome (MTSS) but evidence for its effectiveness is lacking. The primary aim of this study is to determine if the addition of running retraining to best standard care is beneficial in the management of runners with MTSS.

**Methods:**

This study is an assessor‐blinded and participant‐blinded, parallel‐group, randomised controlled trial. The trial will recruit 64 participants aged between 18 and 45 years, with a clinical diagnosis of MTSS that has affected their running participation for at least four weeks. Participants will be randomised to receive best standard care (control) or running retraining and best standard care (intervention group) over an 8‐week period. Best standard care will consist of load management advice, symptom management advice, footwear advice and a strengthening program. Running retraining will consist of a cue to reduce running step length. Outcomes will be measured at weeks 1, 2, 4 and 8. The primary outcome measure will be the University of Wisconsin Running Injury and Recovery Index at week 4. Secondary outcome measures include: (i) Exercise Induced Leg Pain Questionnaire—British Version, (ii) global rating of change scale, (iii) worst pain experienced during a run, (iv) weekly run volume, (v) reactive strength index score, (vi) single leg hop test, (vii) soleus single leg maximum voluntary isometric contraction, (viii) gastrocnemius single leg maximum voluntary isometric contraction, (ix) single leg plantar flexor endurance test, (x) running step length, and (xi) running step rate. Data will be analysed using the intention‐to‐treat principle.

**Discussion:**

This randomised controlled trial will evaluate if reducing running step length provides additional benefit to best standard care in the management of runners with MTSS over an 8‐week period.

**Trial registration:**

Australian New Zealand Clinical Trials Registry: ACTRN12624000230550.

AbbreviationsATEMPTadherence to exercise for musculoskeletal pain toolBMIbody mass indexCVcoefficient of variationEILPQ‐Brexercise induced Leg pain questionnaire (British version)MTSSmedial tibial stress syndromeMVICmaximum voluntary isometric contractionNPRSnumeric pain rating scaleRIRrepetitions in reserveRPErate of perceived exertionRSIreactive strength indexUWRIuniversity of wisconsin running index

## BACKGROUND

1

Medial tibial stress syndrome (MTSS) is one of the most common running‐related injuries, with an incidence as high as 16% [1, 2]. Medial tibial stress syndrome is typically characterised by exercise‐induced pain along the distal posteromedial border of the tibia [2]. The aetiology of MTSS remains uncertain, with traction periostitis from deep crural fascia and failure of tibial bone remodelling both being suggested as possible causes [2]. As running participation provides many health and social benefits, running‐related injuries such as MTSS can result in reduced or ceased physical activity, incur financial costs, and adversely affect an individual's health.

Considering the prevalence of MTSS, interventions that minimise the reduction of running volume or enable a timelier return to usual running volume are sought by clinicians and the wider running community. There is a lack of evidence for effective interventions for the management of MTSS [2]. Despite this, commonly used treatment strategies include running retraining, lower limb strengthening, rest, stretching, massage, graded running programs, shockwave, and injection‐based therapies [2]. Whilst the evidence regarding effective management of MTSS may be scarce, and with the aetiology remaining uncertain, interventions that reduce tibial loads and improve the capacity of the tissues that attenuate tibial loads are proposed to have a positive effect on symptoms.

Running retraining is advocated by most expert clinicians in the management of MTSS, with strategies intended to reduce impact loading being the most common (e.g., reducing overstride, increasing step rate, transitioning to a midfoot strike) [3]. Several running retraining cues can reduce tibial loads [4, 5, 6, 7], but not all cues provide the same effects [4]. In a probabilistic model, running with a reduced step length decreased the likelihood of tibial stress fracture [5], an injury related to MTSS. To date, evidence to support the use of running retraining for the management of MTSS is lacking as no trials have been conducted to determine clinical effectiveness.

Therefore, the primary aim of this study is to determine if the addition of running retraining, by reducing step length, to best standard care, is beneficial in the management of MTSS in runners.

## METHODS

2

### Study design

2.1

The RUNMETRES (RUNning retraining for MEdial Tibial tRESs) study is a parallel‐group randomised controlled trial conducted over an 8‐week period. Participants will be randomised to a control group (best standard care) or an intervention group (best standard care and running retraining). To ensure allocation concealment, permuted block randomisation with random block sizes, stratified by sex at birth will be undertaken using www.sealedenvelope.com. The investigator responsible for recording the outcome measures will be blinded to participants' group allocation. Participants will be blinded to their treatment allocation via limited disclosure, and precautions will be taken to ensure they are unaware of the other treatment group. The trial has been registered on the Australian New Zealand Clinical Trials Registry (ACTRN12624000230550). The findings from the trial will be reported according to the Consolidated Standards of Reporting Trials (CONSORT) statement [6, 7] and the Template for Intervention Description and Replication checklist [8].

### Ethical approval

2.2

Ethical approval for this study was provided by the Human Studies Ethics Committee at La Trobe University (HEC23408). All participants will provide written informed consent prior to their participation. Ethical standards will adhere to the National Health and Medical Research Council National Statement [9] and the World Medical Association's Declaration of Helsinki [10].

### Setting and eligibility criteria

2.3

The trial will be conducted at a private community‐based physiotherapy practice (The Injury Clinic, Geelong, Victoria, Australia) and participants will be recruited via:(i)mail‐out advertisements to local medical and allied health practitioners(ii)social media advertising campaigns(iii)posters displayed in local health and fitness related businesses(iv)contact with local sporting, running and athletic clubs

To be included in the study, participants will be required to meet the following inclusion criteria:(i)aged 18–45 years(ii)have a clinical diagnosis of MTSS; according to subjective history and clinical examination [11]:▪presence of exercise‐induced pain along the tibial periosteum▪pain provoked by (during or after) physical activity and reduced with relative rest▪diffuse tenderness on palpation of the tibial periosteum(iii)have running as a primary exercise activity, participating in running ≥ twice per week(iv)have a history of MTSS that has affected their running activity for ≥ 4 weeks(v)have pain consistent with MTSS rated ≥3 out of 10 on a numeric pain rating scale (NPRS)(vi)be willing to commit to an 8‐week strengthening program that requires completion a minimum of twice per week(vii)be agreeable to not receive any other forms of treatment for the duration of the trial(viii)have an ability to understand written and spoken English

Exclusion criteria for participants in this study will include:(i)any co‐existing lower limb injury in the past 3 months that limits running participation(ii)an inability to attend the required follow‐up sessions(iii)the presence of any symptoms suggestive of alternate lower leg pathology inclusive of stress fracture; cramping or burning pain; paraesthesia; severe swelling or erythema(iv)an inability to run due to the severity of symptoms

### Sample size

2.4

Sample size was calculated based on the primary outcome measure, the University of Wisconsin Running Injury and Recovery Index (UWRI) [12]. Using a power of 80%, previously reported standard deviation of 6.7 [13], medium effect size (Cohen's *d* = 0.75) of 5 points on the 36‐point UWRI [14] and a significance level set at *α* < 0.05, we estimated using GPower 3.1 (Kiel University, Germany) that a total of 60 participants (i.e., approximately 30 per group) will be required. When estimating sample size we were limited with data available and have opted to use the medium effect size for our estimation. To allow for any imprecision in these estimates, we will have a recruitment target of 32 participants per group.

### Interventions

2.5

Participants will be randomly allocated to a control group (best standard care) or an intervention group (best standard care and running retraining).

### Best standard care

2.6

All participants will receive best standard care, consisting of:

#### Load management advice

2.6.1

Participants will be instructed to ensure a pain level of no more than a 2 out of 10 during a run, reported on a NPRS. At the commencement of the trial an individual run program will be discussed with [name] ([name]), with the first 2 weeks not progressing in frequency, volume, or intensity to allow adaptations to the addition of strength training. Following the first two weeks of the trial, weekly running volume will be progressed between 10% and 30% depending on the run training history, time availability, running goals and symptom behaviour of each participant. Weekly running progressions will be programmed and discussed with [name] at week two and week four follow up sessions to ensure an appropriate progression of load for each participant. Participants' running intensity will not be able to exceed a moderate intensity, rated as 6 out of 10 on an 11‐point Borg Scale (0–10) (“labored breathing, challenging and uncomfortable, but sustainable for 30–60 min”) throughout the duration of the trial [15]. Running intensity will be discussed with [name] and details included in weekly run program progressions. If participants experience an exacerbation of their symptoms following a run, they are to report this to [name] and rest until their symptoms have returned to ‘usual’ levels before running again. Their next run is to be completed at an intensity no greater than 4 out of 10 on an 11‐point Borg Scale (“still comfortable, able to hold a conversation”) [15]. If participants experience an exacerbation of their symptoms post‐run over two consecutive run sessions, they are to contact [name] and a modification to their running program will be discussed based on both the severity and time of onset of their symptoms.

The following criteria will be used to guide the progression of each participants running load:(i)volume will be programmed in minutes; with weekly progressions not exceeding 30%(ii)intensity will be programmed using rate of perceived exertion (rate of perceived exertion (RPE)) and rated using an 11‐point Borg Scale (0–10) [15]; intensity minutes will be calculated (*RPE  x minutes*) and monitored, with weekly progressions not exceeding 30%(iii)frequency can be progressed, provided volume progressions do not exceed 30%(iv)terrain is not to be progressed, and participants are to continue to run on their usual terrain (i.e., surface, elevation etc.)

#### Symptom management advice

2.6.2

If participants have been using oral or topical medicines (e.g., analgesia, anti‐inflammatories, etc.) to assist with managing their symptoms, they will be advised to continue with their usual use of medicines. If they have not been using medicines in the management of their symptoms, they will be instructed to not commence using medicines to manage their symptoms during the trial. Participants will be requested to document all use of medicines used to manage MTSS symptoms.

Participants will be instructed on the use of a foam roller/release ball on their posterior lower leg muscles. They will be advised to do this a minimum of twice per week, spending approximately 5 minutes on each leg.

#### Footwear and foot orthoses advice

2.6.3

Participants' running footwear, and foot orthoses if being used for running, will be assessed to determine if appropriate in the opinion of [name] (e.g., running footwear is not showing signs of excessive wear [either on visual observation of the sole of the shoe, or on assessment of foam to ensure no areas of significant collapse]; orthoses have not been recently prescribed, or the participant reports an increase in symptoms or discomfort whilst wearing orthoses). If considered appropriate, participants will be advised to continue to run in the same footwear and foot orthoses for the duration of the trial. If their running footwear is determined to require replacement due to excessive wear, or it is determined to require replacement during the trial, it will be recommended that participants purchase the same footwear model. If the same footwear model cannot be sourced, then a similar replacement model will be recommended following discussion with [name].

#### Strengthening program

2.6.4

The strengthening program will be accessible via a custom‐built software (The Injury Clinic Pty Ltd., Geelong, Australia) installed on their phone using a personal login, inclusive of videos and written instructions of the exercises to be performed. Strength programs will be progressed every 2 weeks, however the load of a specific exercise can be progressed within each program according to the prescribed dosages. For exercises to progress, participants will be instructed to ensure a pain level of no more than a 2 out of 10 as rated on an 11‐point NPRS. Participants will be instructed to determine the load of each exercise based on self‐perceived exertion, this will be done through the programming of Repetitions in Reserve (RIR) and, or Rate of Perceived Exertion (RPE). Due to the inclusion of both isometric and isotonic based movements within this program, both RPE and RIR will be used. The program will be structured with exercises in order of priority to complete, and exercises prescribed in groups of two, ‘superset’ together to assist in a timely completion of prescribed exercises. Full details of the strengthening program are provided in Supporting Information S1.

### Running retraining

2.7

Participants in the intervention group will receive running retraining in addition to best standard care. Running retraining will include a cue to reduce their running step length. Participants will be instructed to shorten their step length by the verbal cue to “land with your foot closer in and under your body”. Compliance with this cue will be assessed with 2D video footage demonstrating a change in lower limb alignment at initial contact. Participants will be issued a Garmin running watch (Garmin Corporation, Olathe, Kansas, USA) that supports the measurement of wrist‐based running dynamics. It will be used to record their preferred running step rate and their step rate when running with the cue for a shorter step length. Although the cue provided to participants will be to “land with your foot closer in and under your body”, the mode of feedback whilst running will be haptic, via the GPS watch, and associated with the step rate recorded when successfully implementing the cue for a shorter step length. For each participant, their Garmin running watch will be setup to provide haptic feedback when they deviate from the target running step rate.

An assessment of participants' running gait will be performed at follow‐up sessions in weeks one, two and four to ensure compliance with the running retraining cue, and they will be provided with real‐time feedback on their running step length and their implementation of the running retraining cue via 2D video footage. Their targeted running step rate (i.e., step rate required to achieve a shortened step length) will be checked and adjusted if needed to ensure the best possible feedback is provided between sessions.

The feedback protocol will be as follows:

*Week 1 and 2* (*acquisition phase*): Haptic feedback will be provided via participant watches during all runs; 2D video feedback will be provided at baseline, week one and week two.

*Week 3 and 4* (*acquisition phase*): Haptic feedback will be provided via participant watches during all runs; 2D video feedback will be provided at week four.

*Week 5 and 6 (transfer phase)*: Intermittent feedback will be provided during runs, with self‐controlled feedback on alternate running sessions.

*Week 7 and 8 (transfer phase)*: No haptic feedback will be provided during runs in the final 2 weeks.

### Assessments and data collection sessions

2.8

Once participants are determined to be eligible for this study, they will undergo primary and secondary outcome measurements at baseline, 2 weeks, 4 weeks, and 8 weeks. Participants will attend five data collection sessions: session 1 (baseline), session 2 (week one), session 3 (week two), session 4 (week four) and session 5 (week eight). Participants in both groups will receive similar time at each data collection session, with the duration of each session measured for comparison at the end of the trial. Figure 1 outlines the flow of participants through the trial.

**FIGURE 1 jfa212029-fig-0001:**
[figure not shown]
Proposed flow of participants through the trial.

### Session 1 (baseline)

2.9

A clinical examination will be performed to ensure that participants have a clinical diagnosis of MTSS [2]. Participants will complete a questionnaire to obtain information concerning the presentation of their symptoms (lower limb affected, duration of symptoms). Participants' age, sex, gender, height, and mass will be recorded. Data regarding running participation (current running volume, running training history) will also be obtained. During the baseline assessment, participants will have primary and secondary outcome measurements (see ‘outcome measures’ section for details regarding all outcomes) collected prior to being allocated to their intervention.

Participants will receive the first 2 weeks of their strengthening program, with exercises demonstrated by [name] ([name]). Participants will then be supervised completing each exercise to ensure appropriate technique and safe execution of the program. Instructions regarding the determination of exercise dosage will be given. Participants will be provided with a Garmin running watch for the duration of the trial if they do not own one that meets the needs of the study. Participants in both groups will have 2D video footage of their running collected. Participants allocated to the intervention group will be receive a running retraining intervention to reduce their running step length, and a step rate target for overground running will be determined. The target step rate will be programmed into participants Garmin watch to enable real‐time feedback. No further instructions will be provided to participants allocated to the control group; however, they will be instructed that we will be documenting how their running mechanics change throughout the duration of the trial.

Participants will be instructed on the use of software, as described previously, to record adherence with their strengthening program and how to document their symptom management strategies (e.g., ice, oral medications, etc.). They will also be given further information regarding the secondary outcome measure ‘worst pain experienced during a run’ to be recorded on a NPRS. Participants will discuss their current symptoms and run load with [name], and an appropriate run program for the first 2 weeks will be outlined.

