### Session 2 (week one)

2.10

At this session, participants in both groups will have their running gait assessed via 2D video. Participants in the intervention group will be provided with real‐time feedback on their running step length. If required, modifications will be made to the step rate feedback for participants in the intervention group to help achieve the desired step length. Participants will also have an opportunity to seek any clarification regarding their strengthening program and symptom management advice.

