#### Step rate

2.14.11

Step rate during running will be recorded using Garmin running watch that support the measurement of wrist‐based running dynamics. Measurements of step rate with Garmin running watches have been shown to be valid and reliable (ICC = 0.931) [26]. In addition, participants' running step rate will be manually counted and recorded over four separate 30‐s intervals during follow‐up sessions. Step rate will be recorded as number of steps per minute.

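### The message described only for controls presupposes that their gait will change; one neutral statement, worded identically for both arms, would remove an avoidable prompt (minor)

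*Protocol article*

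**What the plan says.** Section 2.9 (Session 1) sets out what each arm is told about gait once allocated. The intervention arm receives the retraining and a step rate target. For the other arm, "No further instructions will be provided to participants allocated to the control group", with one qualification: "they will be instructed that we will be documenting how their running mechanics change throughout the duration of the trial".

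The measurement conditions are shared. At baseline, "Participants in both groups will have 2D video footage of their running collected", and sections 2.10 to 2.13 repeat the filming for both groups at weeks 1, 2, 4 and 8. On a suitable watch, section 2.9 says: "Participants will be provided with a Garmin running watch for the duration of the trial if they do not own one". Section 2.14.11 (Step rate) says: "Step rate during running will be recorded using Garmin running watch". Section 2.14.12 derives step length from it as speed divided by step rate.

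On blinding, section 2.1 says: "Participants will be blinded to their treatment allocation via limited disclosure, and precautions will be taken to ensure they are unaware of the other treatment". Separately, the Discussion (section 4) expects the two arms to have nearly the same experience apart from running retraining. It relies on the active comparator to account for placebo and Hawthorne effects.

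**The concern.** The sentence does more than explain the camera and the watch. To say that the trial is documenting how mechanics change implies that change is expected, and running mechanics are what the intervention acts on. As described, it is the only message about gait that controls receive, and the intervention arm is not said to hear it.

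These runners are in pain, and the article itself describes retraining as common in managing this condition. Some may try running differently after hearing the sentence. If they drift towards what the intervention arm is taught, the trial compares retraining with partial self-retraining, and the UWRI difference shrinks for a reason unrelated to whether retraining works.

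**Working it through.** No figure in the plan turns on this point, so the check is a comparison of the relevant sections. The nearest figure is the sample size in section 2.4. It reproduces: 5/6.7 = 0.746, and a two-sample t test at 80% power needs 30 per group, or 60 in total. A two-sided 5% level is assumed, because the article does not state sidedness. Nothing below alters that figure.

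1. **Who hears the sentence, and when.** In section 2.9 it follows the statement about participants allocated to control and refers to them. Baseline outcomes are taken before allocation; this message comes after it. No equivalent sentence is described for the intervention arm.

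2. **What it conveys.** It mentions running mechanics, change, and observation over the whole trial. It does not mention step length, step rate, a direction, a target, a cue or another group.

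3. **What the arms share.** Both are filmed at all five sessions and both run with a suitable watch. Being observed is therefore common to the arms. The statement that change is being documented is not.

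4. **Whether the comparator argument covers it.** The Discussion's reasoning on Hawthorne effects works for a response to attention that is similar in both arms, because it cancels in the difference. It does not work if the response is a gait change in controls. Gait is what the intervention manipulates, so such a change alters the contrast itself.

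5. **Direction.** A shift towards shorter steps would narrow the contrast if it brought benefit. Undirected experimentation could equally have no effect or make symptoms worse. The article gives no rate, direction or effect for unprompted gait change, so neither the size nor the sign of any bias can be derived.

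6. **Whether it would be seen.** Step rate and step length are secondary outcomes, recorded by each participant's watch. Sections 3.1 and 3.2 provide for group comparisons of the outcomes. Drift among controls could therefore be seen, though seeing it would not undo it. Section 2.15 confirms reduced step length as adherence to the intervention; nowhere does the article say that control-arm change will be read as a contamination check.

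**The case against.** The strongest reply is that the sentence does useful work. Controls are filmed repeatedly and may be handed a watch; without some reason they might guess more. A generic explanation is how limited disclosure operates. Controls receive no cue, target or feedback, so saying they are invited to change gait is inference. All of this stands. It supports having an explanation, but not one that presupposes change or that differs between arms.

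Three stronger readings are tempting, and the documents do not support them.

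- **That the sentence breaks the participant blinding.** A reader might set it against section 2.1 and see a contradiction. But it discloses no other arm, technique, direction or hypothesis, so it is compatible with that section. The Discussion also already names participant blinding by limited disclosure as a limitation.
- **That a definite amount of power is lost.** One could suppose that a share c of controls gains the full 5-point benefit and write the expected difference as 5(1 − c). No value of c can be taken from the article. Full benefit is also hard to assume: section 2.7 describes an individual target, haptic feedback on every run in weeks 1 to 4 and repeated video feedback, and controls have none of these.
- **That controls can watch their step rate and should have it hidden.** The article does not say what control watches display, and such settings are commonly left to the full protocol. Some participants will already own a suitable watch. Removing fields from it could itself signal what is being studied.

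**Conclusion.** The point holds in a limited form. The message is described for controls only, comes after allocation, and is worded as though gait will change. It sits poorly with the stated aim that the arms differ only in retraining, and the Discussion's comparator argument would not cancel a real gait change in controls.

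The consequence is a possible contamination of unknown size and uncertain direction. It would narrow the contrast only if controls moved the same way as the intervention arm and benefited from doing so. Nothing is miscalculated, the sample size is unaffected, and the blinding statement is not contradicted. Severity is minor. The point is worth acting on because the remedy costs almost nothing and has to be in place before participants hear the sentence. It assumes that the script in use follows the article's description and that the intervention arm is not given the same sentence.

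**What to change.** Replace the control-arm sentence with one neutral statement that does not mention change, given in identical words to every participant before allocation is revealed. For example: *we will record your running at each visit*.

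Interpret the primary UWRI result alongside the control-arm change in step rate and step length, as a contamination check. Read the two together: step length is speed divided by step rate, so it can move with pace alone. Treat the check as descriptive. These are measurements after randomisation, and control gait may also change as symptoms ease or strength improves, so they should not be used to adjust or exclude participants from the intention-to-treat comparison.

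The cost is a small change of script and a slightly less specific explanation to controls for the filming and the watch. No new data, visits or participants are needed.
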